### Randomization

Randomization occurs after the baseline evaluation. The study statistician ([name]) randomizes assignments using a sequence randomly generated in the R statistical package [41]. These assignments are then sent to a study staff member other than the study coordinator or principal investigator, who puts them into sealed, opaque envelopes with date and signature labels placed over the seals of the envelopes. The study coordinator then contacts eligible participants by phone, and confirms that each one still wishes to participate in the study and is able to make the time commitment to either intervention group. Upon confirmation, the study coordinator opens the consecutive randomization envelope and informs the individuals of their group assignments. The study coordinator also informs the participants of the schedule for their training sessions (including date and time). Randomization envelopes are not opened unless a participant meets eligibility criteria, completes the informed consent, and undergoes a baseline assessment.

The study is conducted in six different cycles. Each cycle consists of an aerobic exercise intervention group and two of the four Tai Chi intervention groups. The Tai Chi intervention groups are rotated through the six cycles so that each one (12 or 24 weeks of supervised Tai Chi, once or twice per week) occurs three times over the course of the study. We use a factorial arrangement to ensure that each of the three Tai Chi instructors conducts each of the four treatments (Tai Chi once or twice per week for each of 12 and 24 weeks) once during the trial. This arrangement is subject to the constraints that two sessions are given in each of the six cycles, that each instructor teaches twice in each of the first three and last three cycles, that no instructor teaches more than once in any single cycle and that each treatment is given at least once and no more than twice in the first three sessions and in the last three sessions. Each instructor is therefore idle for two of the six sessions. The design for each of the four treatments (A, B, C and D) is listed in Table 3. The instructors are randomly assigned to be I, II or III, and each of the four treatments is randomly assigned to be A, B, C or D. Each resulting group consists of 12 patients, for a total of 36 patients participating in each cycle and 216 over the course of the six cycles comprising the study.

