### Sample size

We propose to enroll 216 participants, 144 in the Tai Chi group and 72 in the aerobic exercise group. Power analyses are based on hypothesized changes in FIQR total scores. We used the outcomes of two previous randomized trials to formulate expected effects. Both studies used education controls. The first study by Rooks and colleagues [73] compared the effects of a 16-week aerobic and flexibility exercise program with an education group among 101 participants with fibromyalgia. They found that the aerobic and flexibility exercise group had a 7.9-point mean improvement in the Fibromyalgia Impact Questionnaire (FIQ), yielding an effect size of 0.62. The second study, our pilot trial of 66 participants with fibromyalgia, compared 12-weeks of Tai Chi with a wellness education control [40]. We found an 18.4-point mean improvement in the FIQ score in the Tai Chi group, yielding an effect size of 1.04. We hypothesize that patients receiving Tai Chi will improve more than those receiving aerobic exercise. Using a two-sided hypothesis test at a 0.05 significance level with an allocation ratio of 2:1, a total sample size of 216 (144 in the Tai Chi group, 72 in the aerobic exercise group) would give about 80% power to detect a conservative effect size of 0.4.

We also seek to elucidate how four different schedules of dose and frequency might modify the impact of Tai Chi. With 36 individuals per group, we would have 80% power to detect an effect size of 0.67 between two of these groups with a two-sided 0.05 level test. We will also gain power from the additional individuals tested in the other groups as well as from the blocking by instructor.

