### Data analysis

The primary outcome (change in FIQR between baseline and 24 weeks) will be compared between the five treatment groups using intention-to-treat with a two-sided significance level set at 5%. Participants who withdraw will be treated as having no change from baseline at all times after dropping out. The primary analysis will be a mixed model analysis of variance adjusting for the random blocking factor of instructor. If any characteristics differ substantially at baseline, we will adjust for them in a mixed-model regression analysis. To protect against multiple comparisons, we will only evaluate between-group differences if the overall effect of treatment is significant. If so, we will examine the following contrasts: 1) Tai Chi (four groups) versus aerobic exercise; 2) Tai Chi (12 weeks) versus Tai Chi (24 weeks); 3) Tai Chi once per week versus Tai Chi twice per week; and 4) interaction of number of treatments per week and length of treatment. We will also examine whether treatment effects differ by instructor.

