Secondary analyses will examine change in FIQR from baseline to 12 and 52 weeks as well as secondary outcomes for change at 12, 24, and 52 weeks. Continuous outcomes will be compared by linear regression, and discrete outcomes by logistic regression. All analyses will follow the template for the primary outcome in the previous paragraph, using mixed models with adjustment for instructor examining treatment duration and frequency. If the instructor effect is not significant, we will present results summarized across instructors. All regression models will be assessed by regression diagnostics for adherence to model assumptions. To explore potential psychological and psychosocial mediators (for example, depression, self-efficacy, social support) that may be useful in future research, we will examine treatment interactions with a list of pre-defined moderators. To control for multiple testing, we will perform these tests at a conservative significance level adjusted for the number of moderators tested. In addition, we will also perform longitudinal analyses in which measurements at baseline, 12, 24, and 52 weeks are jointly analyzed using appropriate mixed models including time as a categorical fixed factor with random intercepts and first-order autocorrelation of the errors. Similar mixed models will be used to examine the weekly FIQR measurements taken in the intervention period. We will also check for potential confounding and interaction between time, treatment, instructor and other significant covariates. In addition to intent-to-treat analyses in which dropouts are treated as having no effect, we will also perform secondary analyses using multiple imputation and checks of the mechanism by which participants drop out to determine whether ignorable or nonignorable missing data methods are required [74,75]. If nonignorable methods are needed, we will explore both selection and pattern-mixture types [74,75].

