## Discussion

In this project, we are conducting the first randomized comparative effectiveness trial of Tai Chi versus aerobic exercise in a large fibromyalgia population with long-term follow-up. We present here the plan for a robust and well-designed trial to determine the optimal frequency and duration of a supervised Tai Chi intervention in relation to short- and long-term effectiveness.

Emerging evidence suggests that Tai Chi mind-body exercise has potential therapeutic benefits for fibromyalgia.

Specifically, prior studies have shown that 12 weeks (once to twice per week) of Tai Chi or aerobic exercise is the minimum intervention and practical length needed to achieve effective benefits, especially among beginners [13,14,22,23,26,40]. Further, patients with fibromyalgia have also benefited from 24 weeks of Tai Chi but it is unclear if this longer duration offers better results than a 12-week program.

Hence, the optimum dose and length (frequency or duration) of supervised Tai Chi practice as a treatment for fibromyalgia have not yet been conclusively determined. Optimal clinical implementation remains unknown. In this study, we are comparing 12 weeks of supervised Tai Chi versus 24 weeks of supervised Tai Chi, at two frequencies (one or two times per week), to determine the optimal dose and length of supervised Tai Chi needed for clinical application, compared to 24 weeks of supervised aerobic exercise. We propose to determine the effectiveness of Tai Chi exercise compared to aerobic exercise as well as its clinical utility in a larger scale study over a longer period of time. In addition, testing durability of the supervised exercise up to 52 weeks based on prior data will provide much needed treatment information.

Moreover, investigating multiple secondary outcomes will elucidate the potential mechanisms of mind-body effects. To address one of the unanswered questions from our previous studies about whether the observed benefit of Tai Chi was localized to the instruction of a single instructor or whether the observed benefit could be generalized to others. Systematic differences across instructors would imply that the amount of treatment benefit might depend on the skill level of the individual instructor; lack of differences would imply that the benefit might apply more generally.

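### A non-significant test on three instructors decides whether results are shown only pooled, and it is too weak to show that instructors are alike

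*Protocol article*

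**What the plan says.** All of this is in the protocol article.

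- **Design.** Under Randomization and Table 3, "each of the three Tai Chi instructors conducts each of the four treatments" once, in classes of 12. The layout is built around the instructors.
- **Primary model.** Data analysis puts instructor into the mixed model as a random blocking factor, with no condition attached. It adds: "We will also examine whether treatment effects differ by instructor".
- **Secondary analyses.** The next paragraph says these follow the same template, with mixed models that adjust for instructor. The rule at issue comes straight after: "If the instructor effect is not significant, we will present results summarized across instructors".
- **Interpretation.** The Discussion raises the question, left open by the team's previous studies, of whether benefit was tied to a single instructor. Systematic differences would suggest dependence on instructor skill, whereas "lack of differences would imply that the benefit might apply more generally".
- **Sample size.** Power is given for Tai Chi against aerobic exercise and for pairs of Tai Chi regimens. Instructor appears only as a blocking factor that adds power. No power, margin or interval is given for the instructor question.

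**The concern.** The rule lets a preliminary significance test choose what readers see. If the test is significant, instructor differences come into view; if not, results are presented only in summary. The Discussion then gives an absence of differences a positive meaning, and the article names no criterion for that absence other than the significance test. A non-significant result is evidence of similarity only if the test would probably have found a difference that matters.

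At stake is whether the trial can say anything about benefit across instructors. The abstract lists this among the things the trial explores, and it is the reason for the rotation in Table 3. If the test is weak, the likely outcome is a non-significant result, no instructor-specific figures in print, and a hint of generalisability that the data cannot carry.

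**Working it through.** **Inputs from the article**
- Level: "two-sided significance level set at 5" per cent. No other level is stated, so it is taken for the instructor test too.
- Size: 144 Tai Chi and 72 aerobic participants.
- Three instructors, each with four classes of 12: 4 × 12 = 48 Tai Chi participants per instructor.
- Target effect 0.4 SD for Tai Chi against aerobic exercise.

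**Assumptions.** No dropout, participants as the unit of analysis, and effects in SD units of the outcome. The article gives no instructor intraclass correlation (ICC). Where one is needed, 0.02 to 0.10 is assumed.

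**1. The article's own power figures**
- "would give about 80% power to detect a conservative effect size of 0.4": SE = √(1/144 + 1/72) = 0.1443; 0.4/0.1443 = 2.77; power = Φ(2.77 − 1.96) = 79.1% (78.8% by noncentral t). Reproduced.
- "With 36 individuals per group, we would have 80% power to detect an effect size of 0.67 between two of these groups": 0.67/√(2/36) = 2.84; power = 81.1% (80.05% by noncentral t). Reproduced.

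**2. Power of the instructor test for a fixed gap**

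F test on 2 and 138 degrees of freedom (144 − 4 regimens − 2), critical value 3.06. Let R be the gap between the best and worst instructor.
- Third instructor midway (least favourable): noncentrality = 48 × 2 × (R/2)²
- Third instructor level with one end (most favourable): noncentrality = 48 × (2/3) × R²

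| R (SD) | Noncentrality | Power |
|---|---|---|
| 0.3 | 2.16 to 2.88 | 24 to 30% |
| 0.4 | 3.84 to 5.12 | 39 to 50% |
| 0.5 | 6.00 to 8.00 | 57 to 71% |
| 0.6 | 8.64 to 11.52 | 74 to 86% |
| 0.67 | 10.77 to 14.36 | 84 to 93% |

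A gap equal to the trial's target effect is missed in about half to 61% of trials. Gaps of 0.6 SD or more would usually be found.

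**3. What the data can rule out**
- 95% half-width for the difference between two instructors: 1.96 × √(2/48) = 0.40 SD. Even two identical observed means leave ±0.40 SD open.
- At an observed F of 1, where the estimated instructor variance is zero, the upper 95% limit for the ICC is about 0.45.

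**4. The same test with instructors as a random sample (assumed ICC r)**

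Power = P(F > 3.06 / (1 + 48r/(1 − r))): 22%, 42% and 62% at r = 0.02, 0.05 and 0.10. Testing against variation between classes (2 and 6 degrees of freedom) lowers this to 12 to 15% at r = 0.02 and 22 to 31% at r = 0.05.

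**5. Only if the instructor term were dropped**

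SE for Tai Chi against aerobic exercise, for inference beyond these three instructors: √(r/3 + (1 − r)(1/144 + 1/72)), against 0.144 without the term.

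| r | SE with instructor variance | Naive/true | SE too small by |
|---|---|---|---|
| 0.02 | 0.165 | 0.877 | 12% |
| 0.05 | 0.191 | 0.756 | 24% |
| 0.10 | 0.228 | 0.632 | 37% |

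In 40,000 simulated trials per setting, dropping the term after a non-significant test gave a type I error of 8.7%, 14.5% and 23.1% for this comparison, against 5.1% with no instructor variance. For the duration and frequency contrasts, instructor is crossed with regimen and cancels. Omitting it makes those standard errors 1 to 5% too wide, since 1/√(1 − r) = 1.01 to 1.05.

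**The case against.** A reader might infer that a non-significant test removes instructor from the model and so makes the Tai Chi against aerobic interval too narrow. The article does not support this. The rule speaks of how results are presented. The sentence before it keeps the adjustment for instructor, and the primary model includes instructor unconditionally. The narrowing in step 5 needs a reading the text does not state and an ICC it does not give, and it would not touch the dose contrasts. Stating that the term stays in would not be a complete safeguard either. A variance estimate truncated at zero is zero whenever F is below 1, which under the step 4 model happens in about 50%, 43% and 38% of non-significant trials at ICC 0.02, 0.05 and 0.10.

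A reader might also infer that the plan commits to declaring generalisability whenever the test is non-significant. That too goes beyond the text. The Discussion sentence is not an analysis rule, speaks of a lack of differences rather than of a p-value, and is hedged. The article also promises to examine treatment effects by instructor without a significance condition.

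It can fairly be added that 0.4 SD was set for Tai Chi against aerobic exercise, not for instructors, and that larger gaps would usually be detected. Tables by instructor could also be left to a fuller plan.

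These points limit the concern but do not remove it. The significance trigger is written into the article, and the article offers no other criterion for a lack of differences. Hedged wording does not supply the missing evidence.

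**Conclusion.** The concern holds in a limited form. A non-significant instructor test is the stated trigger for summarising across instructors, and the Discussion treats a lack of differences as pointing towards generalisability. With 48 Tai Chi participants per instructor, non-significance does not show that instructors are alike. The fixed-gap figures in step 2 need no assumed ICC. They do assume full follow-up and independent participants, and they use 0.4 SD as a yardstick borrowed from the trial's own power calculation.

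The point concerns presentation and interpretation. It is no evidence that the primary comparison is miscalculated, because the primary model carries instructor unconditionally and nothing in the text says that the term is ever dropped.

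**What to change.** 1. Remove the significance trigger in Data analysis, and state that instructor stays in every model whatever its p-value.
2. Always report Tai Chi results for each instructor, together with the between-instructor differences or the between-instructor SD, with 95% intervals.
3. Base any statement on generalisability on those intervals, and acknowledge that differences of about 0.4 SD between instructors cannot be ruled out. Do not require the intervals to exclude 0.4 SD: with a half-width of about 0.40 SD, even identical observed means would not meet that test.
4. Reword the Discussion sentence so that a lack of significant differences is not offered as support for wider application.

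The cost is a change of wording, one extra table and a more guarded statement on generalisability. The design and sample size do not change.

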Previous trials have demonstrated that Tai Chi, a complex multi-component mind-body intervention can improve both physical health (aerobic cardiovascular fitness, muscle conditioning, and flexibility) and mental health (psychological well-being, life satisfaction, and perceptions of health) in patients with chronic conditions [22-31]. We have also shown that Tai Chi has great therapeutic benefits for individuals with fibromyalgia compared with a control intervention consisting of wellness education and stretching [32]. Furthermore, in recent meta-analysis of seven studies in 391 participants, we found that 6 to 12 weeks of Tai Chi practice improved fibromyalgia symptoms (effect size 0.50, 95% confidence interval (CI) 0.19 to 0.81), pain (effect size 0.45, 95% CI 0.24 to 0.66), and sleep quality (effect size 0.48, 95% CI 0.14 to 0.81), compared with a variety of controls [33]. This preliminary evidence thus merits this proposed long-term study with a larger clinical sample.

We are currently conducting the first comparative effectiveness trial of Tai Chi versus aerobic exercise in a large symptomatic fibromyalgia population. We hypothesize that: 1) participants receiving Tai Chi, as opposed to aerobic exercise, will have greater improvement in fibromyalgia symptom severity, musculoskeletal pain, fatigue and sleep disturbance, physical and psychosocial functioning, as well as health-related quality of life; 2) participants receiving higher frequency supervised Tai Chi (2 times per week) will have greater improvement than those receiving lower frequency supervised Tai Chi (once per week); 3) participants receiving longer periods (24 weeks) of supervised Tai Chi will have greater improvement than those receiving shorter periods (12 weeks) of supervised Tai Chi; and 4) participants who continue Tai Chi will have durable benefits as determined over a 52-week follow-up period. Overall, we aim to demonstrate that, compared with aerobic exercise, Tai Chi is a more effective intervention for fibromyalgia and has clinical utility in a larger scale study and over a longer period of time.

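### The secondary longitudinal model names first-order autocorrelated errors for visits 12, 12 and 28 weeks apart; if the lag is counted in visits, its standard errors can be wrong

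*Protocol article*

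**What the plan says.** The Data analysis section of the protocol article adds a longitudinal analysis to the change-score analyses. In it, "measurements at baseline, 12, 24, and 52 weeks are jointly analyzed using appropriate mixed models", "including time as a categorical fixed factor" and "with random intercepts and first-order autocorrelation of the errors". The text does not give the unit of the lag. It names no unstructured covariance, no visit-specific variances and no robust standard error.

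Three neighbouring statements limit the point:

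- The 52-week analysis that the plan names is separate: "Secondary analyses will examine change in FIQR from baseline to 12 and 52 weeks". It follows the template of the primary outcome, a mixed model for change at one time point with instructor as a random factor. That template has no autocorrelation structure.
- Model checking is planned: "All regression models will be assessed by regression diagnostics for adherence to model assumptions".
- The weekly data get the same kind of model: "Similar mixed models will be used to examine the weekly FIQR measurements taken in the intervention period".

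Durability is the fourth hypothesis in the Background: "participants who continue Tai Chi will have durable benefits as determined over a 52-week follow-up period". The hypothesis is not tied to a model or to a contrast.

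**The concern.** AR(1) in its ordinary form counts lag by visit order. One parameter then has to serve two 12-week gaps and one 28-week gap. If scores 28 weeks apart are less alike than scores 12 weeks apart, the fitted parameter is a compromise: too high for weeks 24 to 52 and too low for the earlier gaps. The variance of a change falls as the correlation rises, so the late change would look more precise than it is and the early changes less precise. The structure also forces equal variances at all four visits.

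With categorical time by treatment and complete data, the estimated means are unaffected. What is at stake is the standard errors, intervals and p-values of this secondary model. The change most exposed is week 24 to week 52, which a reader interested in persistence of benefit after supervised treatment may well look at.

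**Working it through.** **The plan's own figures.** The article gives no correlation, standard error or power for this model. Its only precision figures are in Sample size, and they reproduce by the normal approximation:

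- 144 against 72, effect size 0.4: 0.4/√(1/144 + 1/72) = 0.4/0.1443 = 2.77. Power = Φ(2.77 − 1.96) = 0.79, against a stated figure of about 80%.
- 36 against 36, effect size 0.67: 0.67/√(2/36) = 2.84. Power = Φ(2.84 − 1.96) = 0.81, against a stated 80%.

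Neither figure uses the longitudinal covariance.

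**Inputs.** Visits at 0, 12, 24 and 52 weeks and group sizes of 144 and 72 come from the article. The correlations are assumptions.

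**Assumed truth.** Total variance is 1. A share a is a random intercept, and the rest is error whose correlation decays with elapsed time:

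cov(s, t) = a + (1 − a) r^(|s − t|/12), where r is the error correlation at 12 weeks.

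**Fitted model.** Random intercept plus AR(1) by visit order: A + S ρ^|i − j|. A, S and ρ are the large-sample (Kullback-Leibler) best fit to the assumed truth.

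**One case in full, a = 0.3 and r = 0.5.** The best fit is A = 0.292, S = 0.707, ρ = 0.404.

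- Weeks 24-52. True error correlation 0.5^(28/12) = 0.198, so true variance of change = 2(0.7)(1 − 0.198) = 1.122. Model variance = 2(0.707)(1 − 0.404) = 0.843. SE ratio = √(0.843/1.122) = 0.87.
- Weeks 0-12. True 2(0.7)(1 − 0.5) = 0.700; model 0.843; ratio 1.10.
- Weeks 0-24. True 2(0.7)(1 − 0.25) = 1.050; model 2(0.707)(1 − 0.404²) = 1.183; ratio 1.06.
- Weeks 0-52. True 2(0.7)(1 − 0.5^(52/12)) = 1.331; model 2(0.707)(1 − 0.404³) = 1.321; ratio 1.00.

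For the between-arm difference in 24-52 change, the true SE is √1.122 × 0.1443 = 0.153 SD and the model reports √0.843 × 0.1443 = 0.132 SD (unrounded inputs). The 95% half-widths are 0.300 and 0.260 SD. Actual coverage is 2Φ(1.96 × 0.866) − 1 = 91.0%.

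**Range over r (a = 0.3; other values of a from 0 to 0.6 barely change it).** Ratio of model SE to true SE:

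| r | 24-52 | 0-12 | 0-24 | 0-52 | Coverage, 24-52 |
|---|---|---|---|---|---|
| 0.1 | 0.97 | 1.02 | 1.00 | 1.00 | 94.2% |
| 0.3 | 0.91 | 1.06 | 1.02 | 1.00 | 92.6% |
| 0.5 | 0.87 | 1.10 | 1.06 | 1.00 | 91.0% |
| 0.7 | 0.83 | 1.14 | 1.11 | 1.00 | 89.6% |
| 0.9 | 0.80 | 1.18 | 1.17 | 1.00 | 88.3% |

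**Other assumed truths.**

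- Constant correlation, or correlation that truly follows visit order: every ratio is 1.00.
- Scores more stable after treatment than between baseline and week 12: the 24-52 ratio is 1.07 to 1.11 and coverage 96.3% to 97.1%, so the interval is too wide.
- Baseline SD 0.7 to 0.9 of later visits, with a = 0.3 and exponential decay with a time constant of 24 to 40 weeks: the 24-52 ratio is 0.81 to 0.83, and the 0-52 SE becomes 2% to 9% too large.

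**With the lag in weeks.** Under the decaying truth with equal variances, all ratios are 1.00 and coverage is 95%.

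**The case against.** The strongest reply is that the article never commits to a lag counted in visits. A continuous-time form is also first-order autocorrelation, and categorical time describes the mean, not the lag. This stands, and the point is therefore conditional. It does not remove the point: the article does name a structure, its ordinary form counts visits, and the unequal spacing is not addressed.

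A reader might infer that the plan produces a durability interval that is too narrow. The documents do not support that, for three reasons. No 24-to-52-week contrast is specified. The 52-week change that is named runs from baseline, in a model without autocorrelation, and even inside the longitudinal model its SE is almost right when variances are equal. The direction of the error also depends on a correlation pattern that the article does not give, and greater stability after treatment would reverse it.

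A reader might also infer that entry criteria compress the baseline FIQR variance. Table 2 sets no FIQR threshold, so that is possible but not shown.

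The planned diagnostics are a partial answer. They name no alternative covariance, and any change would be made after the data have been seen.

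No defect appears in the weekly FIQR model. Its measurements are equally spaced, so a lag in visits and a lag in weeks are the same thing.

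**Conclusion.** The point holds in conditional form and is minor. If the lag is counted in visits, the model imposes one error correlation on 12-week and 28-week gaps and one variance on all visits. If correlation decays with elapsed time, nominal 5% tests of a 24-52 change would then run at about 6% to 12% (100% minus the coverages above), while tests of 0-12 and 0-24 change would be conservative. These figures rest on assumed correlations, equal variances, complete data and a saturated time-by-treatment mean. The primary comparison at 24 weeks, the sample size and the named baseline-to-52-week analysis stand as they are. What can be improved is a stated secondary method, at almost no cost.

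**What to change.** For the four-visit model, replace random intercepts plus first-order autocorrelation with an unstructured covariance across weeks 0, 12, 24 and 52, with Kenward-Roger degrees of freedom. Drop the participant-level random intercept, which an unstructured matrix already contains, and keep the instructor term as planned. The matrix has 4 × 5/2 = 10 parameters, which 216 participants can support.

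State the fallback in advance: if the unstructured model does not converge, use a correlation whose lag is measured in weeks. That handles the spacing but still assumes equal variances, so it is second best.

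The weekly FIQR model needs no change on this ground. The cost is one covariance specification and a sentence in the analysis plan, with no new data and no effect on the sample size.

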### Primary outcome

The primary outcome measure is change in the FIQR score between baseline and 24 weeks. The FIQR is a well-validated multidimensional instrument that measures participant-rated overall severity of fibromyalgia, including intensity of pain, physical function, fatigue, morning tiredness, depression, anxiety, job difficulty, and overall well-being [35]. Each item is standardized on a scale ranging from 0 to 10, with lower scores indicating more improvement or less negative impact. In addition, FIQR is also assessed weekly during the intervention period for all groups of participants as well as at the 52-week time points as secondary outcomes.

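### Nonignorable missing-data analyses run only if a check of the dropout mechanism calls for them, but observed data cannot answer that question

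*Protocol article*

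**What the plan says.** The Primary outcome section fixes the endpoint: "The primary outcome measure is change in the FIQR score between baseline and 24 weeks". The Data analysis section then treats missing data in three layers.

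- **Primary rule.** "Participants who withdraw will be treated as having no change from baseline at all times after dropping out".
- **Secondary, without condition.** "we will also perform secondary analyses using multiple imputation". Joint longitudinal mixed models over baseline, 12, 24 and 52 weeks are also planned, with similar models for the weekly FIQR.
- **Secondary, conditional.** The same section plans "checks of the mechanism by which participants drop out to determine whether ignorable or nonignorable missing data methods are required", and continues: "If nonignorable methods are needed, we will explore both selection and pattern-mixture types".

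The article gives no criterion for the check, no expected dropout rate, and no graded nonignorable analysis that runs whatever the check shows.

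**The concern.** Dropout is ignorable, in the sense used here, if the chance of dropping out does not depend on the unseen 24-week score once the recorded data are taken into account. The dropouts' unseen scores are exactly what would be needed to test that. Checks on recorded data can show that dropout is related to baseline or earlier FIQR, which argues against missingness completely at random. They cannot go further and show that nonignorable methods are unnecessary. The plan asks the check for an answer it cannot give, and makes a class of analyses depend on it.

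The possibility is a practical one here. FIQR is participant-rated. The Study design overview names only the physical-function assessors and the statistician as blinded, and the Randomization section has participants told their assignment. Supervised load also differs: 12 to 48 sessions across the Tai Chi groups (once or twice weekly for 12 or 24 weeks) against 48 for aerobic exercise (twice weekly for 24 weeks). Dropout linked to lack of benefit could differ by arm. At stake is whether a reader of the results can see how far the Tai Chi versus aerobic exercise contrast depends on what is assumed about dropouts.

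**Working it through.** **The plan's own figure.** The Sample size section states that 144 and 72 participants, tested two-sided at 0.05, "would give about 80% power to detect a conservative effect size of 0.4". The standard error in SD units is √(1/144 + 1/72) = 0.144. Then 0.4/0.144 = 2.77, and 2.77 − 1.96 = 0.81, which gives 79.1% power (78.8% with the t distribution). The figure reproduces, and nothing below alters it.

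**Can a check on observed data tell the cases apart?** One group of 400,000 was simulated, with dropout depending on baseline only. The dropouts' unseen outcomes were then shifted by 0, 0.3, 0.6 or 1.0 SD.

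| Shift in dropouts (SD) | Dropout | Observed mean | Observed slope | Residual SD | True full mean |
|---|---|---|---|---|---|
| 0 | 20.9% | −0.049 | 0.502 | 0.999 | −0.001 |
| 0.3 | 20.9% | −0.049 | 0.502 | 0.999 | 0.062 |
| 0.6 | 20.9% | −0.049 | 0.502 | 0.999 | 0.125 |
| 1.0 | 20.9% | −0.049 | 0.502 | 0.999 | 0.208 |

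Everything observed is identical by construction, including the fitted dropout model, while the true mean moves by about 0.21 SD. No check on the observed columns can separate the rows.

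**Size of the shift in the contrast.** Let d be the share of dropouts in an arm and δ the amount, in SD of change, by which they do worse than imputed. The contrast in improvement, Tai Chi minus aerobic exercise, falls from its imputation value by

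(d_TC × δ_TC) − (d_AE × δ_AE).

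All values of d and δ are assumptions.

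- Tai Chi dropouts only, δ = 0.5: 0.10 × 0.5 = 0.05 and 0.20 × 0.5 = 0.10. Relative to 0.4, these are 12.5% and 25%.
- Tai Chi dropouts only, δ = 1: 0.10 and 0.20, or 25% and 50%.
- Equal d and equal δ in both arms: zero.

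Against the standard error above, 0.05 to 0.10 is about 0.35 to 0.69 standard errors.

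**Do the two unconditional analyses bracket the answer?** Assume completers improve by 1.0 SD on Tai Chi and 0.6 SD on aerobic exercise, so that imputation gives 0.40. The no-change rule gives 1.0(1 − d_TC) − 0.6(1 − d_AE).

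| Dropout TC / AE | Imputation | No change | Both arms shifted 0.3 to 1.0 | Tai Chi only shifted 1.0 |
|---|---|---|---|---|
| 20% / 20% | 0.40 | 0.32 | 0.40 throughout | 0.20 |
| 25% / 15% | 0.40 | 0.24 | 0.37 to 0.30 | 0.15 |
| 10% / 30% | 0.40 | 0.48 | 0.46 to 0.60 | 0.30 |

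The last column is 0.40 − d_TC × 1.0. In every row it lies below both unconditional analyses. With a common shift, the two analyses do bracket the result in the first two rows. In the third, the larger common shifts go beyond 0.48, in favour of Tai Chi.

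**The case against.** The strongest reply has four parts.

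1. The article does not say that the check is a statistical test on observed scores. The trial also records reasons for missed sessions (stated for aerobic exercise), weekly adverse events and monthly follow-up calls, and a fuller document may say how the check is done. This stands as a description. But such information can only inform a judgement about the mechanism. No named check would settle it, so the fault lies in the stated rule and not in missing detail.

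2. A reader might infer that the trial's main result would rest on one untested assumption, or that an essential analysis is bound to be lost. The documents do not support that. The conditional models are secondary. The no-change rule and multiple imputation are different assumptions, and both apply whatever the check shows. Comparing them is a real, if coarse, test of dependence. The planned mixed models add little to it: fitted to the data as observed, they too rely on ignorable dropout, and fitted to data filled in as no change, they repeat the primary rule.

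3. Where both arms are shifted alike, the two unconditional analyses often bracket the result, or miss only values more favourable to Tai Chi. That is true of the common-shift examples. It fails once the shift differs by arm, as the last column of the table shows.

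4. Weekly FIQR during the intervention would sharpen the imputation, so a departure of 0.5 to 1 SD beyond a participant's own recorded course is a demanding assumption. This stands, and the upper figures should be read as the far end of a range. The protection is weaker in the 12-week groups after week 12, when weekly collection has ended.

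**Conclusion.** The rule is faulty as written: it makes nonignorable analyses depend on a question that observed data cannot resolve, so a reassuring check could wrongly leave them out. What may be lost is a graded view of departures from ignorable dropout, particularly departures that differ by arm.

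Under the assumed 10% to 20% dropout with a 0.5 SD shift in Tai Chi dropouts only, the contrast moves 0.05 to 0.10 SD from the imputation result, or 12.5% to 25% of the 0.4 target. The movement is zero with equal dropout and equal shifts. Shifts of this size matter mainly for a result near the significance threshold.

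These figures describe bias in the secondary imputation analysis, read in context as the ignorable one. They should not be taken as the bias of the primary no-change analysis, and they do not show that dropout in this trial is in fact nonignorable. The primary test, alpha, sample size and power are unaffected. The change should be made, but it concerns a sensitivity analysis.

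**What to change.** Delete the condition. State that a pattern-mixture (delta-adjusted) multiple imputation of 24-week FIQR will always be run as a secondary sensitivity analysis, with these features:

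- an imputation model that uses the weekly FIQR data;
- separate shifts for withdrawn participants in each arm, over a grid fixed in advance (for example 0 to 1 SD worse than imputed, crossed between Tai Chi and aerobic exercise);
- a report of the combinations of shifts at which the Tai Chi versus aerobic exercise contrast changes its conclusion.

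Keep the dropout checks, but use them only to describe dropout and to inform the grid. Selection models can stay as an optional addition.

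The cost is a small amount of extra analysis and a sentence or two of wording. It needs no new data and changes no sample size, alpha or primary analysis.
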